## Abstract

**Background:**

Approximately 1 in 8 children under the age of 6 in Tamil Nadu are diagnosed with neurodevelopmental disorders (NDD), yet only a fraction of these children receives proper medical care. The unequal distribution of healthcare services is mainly due to the lack of accessibility, especially in rural areas, leading to a significant burden on caregivers. This research aims to alleviate caregiver burden and reduce disability in preschool children by establishing model clinics or specialized outreach centers in rural villages, supported by SRM Institute of Science and Technology under the Unnat Bharat Abhiyan Scheme.(UBA-SRMIST).

**Methods:**

The study will commence with screening all preschool children registered in Anganwadi in the designated villages. Tailored model clinics will be set up in these villages based on the prevalence of NDD. Once established, children diagnosed with NDD will undergo rehabilitation for a year. Baseline and endline assessments will be conducted to evaluate the effectiveness of the model center on both the child's disability and the caregiver burden.

**Discussion:**

This research will demonstrate the effectiveness of a model outreach center in rural villages in reducing disability levels in children and alleviating caregiver burden by eliminating the need for long travels to access rehabilitation services. The findings of this study will not only contribute to the objectives of UBA-SRMIST in uplifting villages but also facilitate the creation of registries and provision of data to the government for the implementation of policies that address the current disparities in healthcare access.

*Trial registration* Trail has been registered under Clinical Trials Registry—India (CTRI/2024/06/069196).

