## Background

Neurodevelopmental disorder (NDD) is a comprehensive term that encompasses a variety of conditions or dysfunctions that impede the growth and/or development of the nervous system, including issues such as visual impairments, specific learning disorders, autism, global developmental delay, Attention Deficit Hyperactivity Disorder(ADHD), Developmental Coordination Disorder (DCD) collectively impacting 13% of pediatric health cases. [1, 2].

Globally, more than 50 million children are recognized as having neurodevelopmental disabilities, with an estimated 23 million Indian children falling into this category, of whom only a small percentage receive medical attention.(2) The increasing prevalence suggests that one in eight Indian children experiences some form of NDD. In Tamil Nadu, it is approximated that 2% of children below the age of 6 have a form of disability, with many of them lacking medical care. [1–4].

The preschool age (3–5 years), which marks a critical period for functional brain development, neuronal migration, and cognitive and behavioral growth, and this group of children remains relatively unexplored. Despite the higher rate and risk of NDD development during this period, there is a lack of focus on it compared to infancy. This could be due to the challenges in screening or imaging assessments, resulting in a shortage of early detection methods. [5].

The alarming prevalence and long-term complications associated with NDD raise concerns regarding the need for specialized care, yet there is a shortage in the implementation of such care. This shortage is attributed to the limited access to specialized healthcare services. Various reasons contribute to this lack of access, including geographical barriers, economic constraints, cultural factors, lack of awareness, inadequate healthcare infrastructure, and insufficient healthcare workforce. [6, 7].

Data from National Family Health Survey (NFHS) II indicates that seven out of ten individuals in India lack access to healthcare, with even higher rates in rural areas as specialists are predominantly located in urban centers. Only one out of ten individuals have access to hospitals, and 13% have access to primary healthcare facilities. [7, 8].

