## Materials and methods

### Participants

A single arm study will be conducted among children aged 3 to 5 years attending Anganwadi centers in SRM UBA adopted villages who will be screened for neurodevelopmental disorders with parental consent. Those identified with NDD or previously diagnosed with any form of NDD will be included in the study.

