The model center, or specialist outreach center, is envisioned to have trained physiotherapists for children's rehabilitation, with pediatric physicians visiting the centers for progress checks and further evaluations. Equipped with essential tools such as swiss ball, peanut ball, obstacle for gait training, balance boards,etc., the center will provide pediatric rehabilitation and group therapies for children. Discussions and arrangements will be initiated with village authorities to position the model center close to or within school/Anganwadi premises.

Subsequent to NDD identification in children, baseline assessments of NDD will be conducted alongside qualitative assessment of caregivers' perspectives and experiences regarding accessing rehabilitation services in the community. Quantitatively, caregiver burden will be evaluated using a caregiver burden scale.

Upon enrollment, children will undergo physiotherapy rehabilitation for one year under a trained physiotherapist, with routine screenings by pediatricians. The neurodevelopmental rehabilitation will include sensorimotor training, motor learning, sensory integration, motor training and neurodevelopmental therapy which will be tailored according to the individual’s needs and the severity and type of disorder. Treatment will be given in person, in group or as individual therapy. The entire timeline and flow have been illustrated in Table 1.

**Table 1 Tab1:** Spirit timeline for the study

	Enrolment and allocation		Post allocation				Endline evaluation	Close-out
Time point	− t1	t0	t1	t2	t3	t4	t5	t7
Preliminary screenings	X							
Parental consent	X							
Analysis of prevalence	X							
Eligibility screen		X						
Obtained signed parental consent		X						
Allocation		X						
Baseline assessments		X						
Establish model centre		X						
One year rehabilitation			X	X	X	X		
Routine follow up screenings by pediatricians			X	X	X	X		
Baseline tools	X	X					X	
Effectiveness of intervention		X					X	
Caregiver burden		X					X	
Data entry and analysis	X						X	
Share findings with authorities	X							X
Final reports								X
Plan future studies								x

Each t indicates 3 months of time span

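### A single-arm, before-after study can describe change over a year at the centre but cannot demonstrate its effectiveness or impact, as the protocol article says it will

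*Protocol article*

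**What the plan says.** The design is stated openly under Participants: "A single arm study will be conducted among children aged 3 to 5 years attending Anganwadi centers in SRM UBA adopted villages". Entry has two routes: "Those identified with NDD or previously diagnosed with any form of NDD will be included in the study". After enrolment, according to Procedures, "children will undergo physiotherapy rehabilitation for one year under a trained physiotherapist".

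The abstract's Methods paragraph gives the contrast: "Baseline and endline assessments will be conducted to evaluate the effectiveness of the model center on both the child's disability and the caregiver burden". Table 1 marks the baseline assessments at t0, and both the effectiveness and caregiver-burden rows at t0 and t5, with rehabilitation over t1 to t4. Its footnote reads "Each t indicates 3 months of time span", so treatment covers 4 × 3 = 12 months. Procedures adds that the endline is assessed by the physiotherapist who gave the rehabilitation.

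Under Statistical analysis, caregiver burden before and after the intervention is compared by t-test. ANOVA compares clinics or regions. A binary logistic regression of reduced burden (yes/no) on covariates is offered as the way to find the intervention's impact.

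The causal claims stand in four places:

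- Abstract, Discussion: "This research will demonstrate the effectiveness of a model outreach center in rural villages in reducing disability levels in children and alleviating caregiver burden".
- Primary objectives: the centre's impact on caregiver burden is to be assessed.
- Statistical analysis: the logistic model is to identify the intervention's impact.
- Discussion: the results are meant to help substantiate the efficacy of outreach clinics.

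**The concern.** A causal statement needs some estimate of what would have happened to these children and caregivers without the centre. A single treated group measured before and after does not supply one. The article itself says that the preschool age "marks a critical period for functional brain development, neuronal migration, and cognitive and behavioral growth", so change over a year is to be expected in this age band whether or not a centre opens. Caregiver burden may also move for reasons unrelated to the centre, and in either direction.

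The claim has consequences. The Discussion presents the study as a possible model for centres elsewhere in Tamil Nadu and as guidance for government. A reader who takes the abstract at its word would credit the centre with the whole of the observed change. If burden did not fall, the same reader might wrongly conclude that the centre failed.

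**Working it through.** The article gives no sample size, effect size or standard deviation, so there is no figure to reproduce. The main check compares design with claim. Two calculations follow, as illustration only.

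**1. Is there any comparator?** Participants declares a single arm. The ANOVA groups are clinics or regions, and no untreated group is described. The t-test contrasts two times in the same caregivers. The planned estimate is therefore the mean change from t0 to t5.

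**2. Can the logistic model isolate the intervention?** Its outcome, a reduction in burden, is a change from before to after treatment, and everyone in the study is treated. An intervention indicator would equal 1 for every record and be indistinguishable from the intercept. Adjusting for socioeconomic status or severity does not alter this. The model can show which caregivers are more likely to report a reduction, not how far the centre caused it.

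**3. What is mixed into the change?** A year of development (child scores); time trends and other care (both outcomes); and endline assessment by the person who delivered the treatment (both outcomes).

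**4. How readily could drift alone look like benefit?** Assume a paired t-test, two-sided 5%, no treatment effect, drift d in SD units and within-person correlation r. The SD of the difference is √(2(1 − r)) and the non-centrality is d√n / √(2(1 − r)). For d = 0.2, r = 0.7 and n = 60: √0.6 = 0.775, and 0.2 × 7.746 / 0.775 = 2.0. All values of d, r and n are assumptions.

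| d | r | SD of difference | n = 30 | n = 60 | n = 100 |
|---|---|---|---|---|---|
| 0.1 | 0.5 | 1.00 | 8% | 12% | 17% |
| 0.2 | 0.7 | 0.775 | 28% | 50% | 73% |
| 0.3 | 0.85 | 0.548 | 83% | 99% | over 99% |

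Entries are the chance of p < 0.05. The wide range shows that the size is unknown; what the table does show is that significance is no evidence of a treatment effect here.

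**5. Does regression to the mean add to this?** If the score that qualified a child were also the baseline, the expected untreated improvement would be (1 − r) × φ(z)/p SD, where p is the fraction selected. Inputs: test-retest reliability 0.85 to 0.95 (ADHD rating scale section), and p of 2% or 12.5%, borrowed from the two prevalence figures in the Background.

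- p = 12.5%: φ(z)/p = 1.647, giving 0.05 × 1.647 = 0.08 SD to 0.15 × 1.647 = 0.25 SD.
- p = 2%: φ(z)/p = 2.421, giving 0.05 × 2.421 = 0.12 SD to 0.15 × 2.421 = 0.36 SD.

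With a fresh measurement after selection as baseline, simulation puts this component within 0.004 SD of zero. Table 1 schedules that fresh measurement at t0.

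**The case against.** **A single arm can be a legitimate choice.** It is openly declared and can serve a descriptive or pilot aim. This stands: the fault lies in the claim attached to the design. The interviews with parents on how the clinic affected burden and access add useful information, but they do not replace a control.

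**A fuller protocol or analysis plan may exist.** It could refine the tests, but it could not add a comparator to a declared single-arm study. Table 1 has an allocation row at t0, but no second group to allocate to is described.

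**Regression to the mean is largely handled.** A reader might infer that the reported change will be inflated by the 0.08 to 0.36 SD shown above. The document does not support that. The figure applies only if the -t1 screening score were the reference, whereas Table 1 places the outcome rows at t0 and t5. Previously diagnosed children can enter without a qualifying score. Screening uses four tools, which selection on a single scale does not represent. Caregivers, who supply the primary outcome, are not selected on burden, so the effect does not reach it directly.

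**The text is not uniformly strong.** A reader might also infer that any improvement would be taken as proof. The article does not say so: the abstract's Methods speaks of evaluating, and the Discussion says only that the study can serve as a blueprint. The abstract's concluding sentence and the stated purpose of the logistic model nevertheless go beyond the design.

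**Conclusion.** The point holds for the causal wording. The study will estimate change in caregiver burden and child scores over one year of attending the centre. The four causal statements attribute to the design something it does not have, and the logistic regression cannot deliver the effect it is assigned.

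This conclusion needs no number and rests only on the stated single arm and the before-after contrast. The size, and for caregiver burden even the direction, of the non-treatment part is unknown; the drift percentages rest wholly on assumed values. The document supports saying that the change cannot be separated from maturation, time trends, other care and unblinded assessment. It does not support saying that a given share of the change is due to them. Regression to the mean is a side issue as long as t0 remains the reference for child scores.

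**What to change.** 1. In the abstract's Discussion, the Primary objectives and the main Discussion, replace the claims of effectiveness, impact and efficacy with *change in caregiver burden and child scores over one year of attending the centre*.
2. Under Statistical analysis, describe the logistic regression as examining factors associated with a reduction in burden among caregivers of treated children, not as estimating the intervention's effect.
3. State as limitations that there is no control group and that the treating physiotherapist assesses the endline.
4. Say in one sentence that t0, as Table 1 already schedules, is the reference score for child outcomes.

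These are wording changes with no added data collection. The price is a more modest conclusion.

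Optionally, give the 15-item Caregiver Burden Scale once more before rehabilitation and report that early change beside the one-year change. This costs one short questionnaire per caregiver. It gives only a short and imperfect view of untreated drift: the gap is probably at most about 3 months (inferred from Table 1, not stated) against 12 months of treatment, and it would start just after the child is identified, when burden may be unsettled.

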**Supplementary Information:**

The online version contains supplementary material available at 10.1186/s41043-024-00686-1.

## Background

Neurodevelopmental disorder (NDD) is a comprehensive term that encompasses a variety of conditions or dysfunctions that impede the growth and/or development of the nervous system, including issues such as visual impairments, specific learning disorders, autism, global developmental delay, Attention Deficit Hyperactivity Disorder(ADHD), Developmental Coordination Disorder (DCD) collectively impacting 13% of pediatric health cases. [1, 2].

Globally, more than 50 million children are recognized as having neurodevelopmental disabilities, with an estimated 23 million Indian children falling into this category, of whom only a small percentage receive medical attention.(2) The increasing prevalence suggests that one in eight Indian children experiences some form of NDD. In Tamil Nadu, it is approximated that 2% of children below the age of 6 have a form of disability, with many of them lacking medical care. [1–4].

The preschool age (3–5 years), which marks a critical period for functional brain development, neuronal migration, and cognitive and behavioral growth, and this group of children remains relatively unexplored. Despite the higher rate and risk of NDD development during this period, there is a lack of focus on it compared to infancy. This could be due to the challenges in screening or imaging assessments, resulting in a shortage of early detection methods. [5].

The alarming prevalence and long-term complications associated with NDD raise concerns regarding the need for specialized care, yet there is a shortage in the implementation of such care. This shortage is attributed to the limited access to specialized healthcare services. Various reasons contribute to this lack of access, including geographical barriers, economic constraints, cultural factors, lack of awareness, inadequate healthcare infrastructure, and insufficient healthcare workforce. [6, 7].

Data from National Family Health Survey (NFHS) II indicates that seven out of ten individuals in India lack access to healthcare, with even higher rates in rural areas as specialists are predominantly located in urban centers. Only one out of ten individuals have access to hospitals, and 13% have access to primary healthcare facilities. [7, 8].

The inequitable access to healthcare further compounds the situation, particularly in rural and economically disadvantaged settings in southern India, increasing the load on caregivers of children with NDD. As caregivers assume a pivotal role in the rehabilitation of children with NDD, their heightened responsibilities/burden directly influence the caliber of care extended to the child. [9, 10].

Primary Health Care (PHC), established to redress disparities in healthcare accessibility in India, has encountered obstacles in fulfilling its goals, especially in rural areas due to inadequate staffing and limited resources. Inadequate monitoring, limited supplies, low community engagement, and subpar care provision underscore the need for a potential alternative and integrated care model. [11, 12].

Considering that enhancing child health and ensuring healthcare for all is a fundamental objective of sustainable development, it is imperative to tackle these concerns underscored in the Astana Declaration of 2018. [13, 14].

WHA Rehabilitation 2030 initiative emphasizes the global need for rehabilitation services, particularly in low- and middle-income countries, and promotes the development of essential frameworks and interventions, this calls in for a enhanced rehabilitation services in low- and middle-income countries like India. [15].

The fragmented nature of the healthcare system and the unequal distribution of healthcare facilities, coupled with limited specialist care, have prompted concerns regarding the need to establish robust and specialized outreach centers that ensure maximum accessibility and utility. [6].

To enhance the utility of outreach clinics, it is advised to establish customized outreach centers tailored to the specific needs of the community, preferably located in schools. School-based healthcare services have been shown to enhance accessibility and utilization, involving various healthcare professionals such as physicians, nurses, physical therapists, occupational therapist, speech language pathologists, community workers, and even teachers. [6].

Previous research has focused on estimating the prevalence of disabilities among preschool children in Western regions, leaving a significant data gap on the challenges faced by caregivers and disabled preterm children in Tamil Nadu. This lack of evidence hampers the development of policies, model outreach clinics, and support systems for parents and guardians of preterm children with disabilities, potentially leading to preventable long-term complications due to delayed access to healthcare and screening.

Given the increasing rate of NDD in early childhood and lack of accessibility it is imperative to regularly screen children for potential risk factors and provide timely interventions to prevent long-term complications particularly in rural areas with limited access to specialist care.

A two-step approach involving screening and definitive testing at healthcare facilities, along with standardized assessments for early identification of developmental abnormalities, is crucial for improving outcomes in children with NDD.

SRM Institute of Science and Technology (SRMIST) Kattankulathur, in alignment with the developmental goals of Unnat Bharat Abhiyan (UBA) has launched UBA-SRMIST in 2019 under the guidance of the University Grants Commission/ Ministry of Human Resource and Development/ All India Council for Technical education. UBA-SRMIST has adopted twelve rural villages in Kancheepuram and Chengalpattu and has conducted several welfare programs including awareness camps, screening programs and providing COVID-19 vaccination.

This study aims to evaluate the developmental outcomes of preschool children in twelve adopted villages of UBA-SRMIST, Kattankulathur, and provide early intervention programs by establishing a specialist outreach/model clinic which will help to uplift the village and generate data that can inform policies and interventions aimed at supporting parents, enhancing accessibility, and reducing the  burden of caregiver.

## Primary objectives

To assess the prevalence of neurodevelopment disorder among children in the UBA adopted villages of SRMIST.

To develop a model physiotherapy centre and assess its impact on reducing the burden among the caregivers of children with neurodevelopmental disorders in rural areas of Tamil Nadu.

## Materials and methods

### Participants

A single arm study will be conducted among children aged 3 to 5 years attending Anganwadi centers in SRM UBA adopted villages who will be screened for neurodevelopmental disorders with parental consent. Those identified with NDD or previously diagnosed with any form of NDD will be included in the study.

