## Procedures

Given the need for a comprehensive understanding of the local community to plan a specialist outreach clinic effectively, this study will be conducted in phases to assess prevalence, healthcare needs, and resource availability. This is crucial for establishing a specialized outreach clinic in a village. [16].

The initial phase of the research will entail the gathering of fundamental data from the twelve villages adopted by SRMIST namely, Kolathur, Chettipuniyam, Orathur, Nattarsanpattu, Anjur, Thenmelpakkam, Pattaravakkam, Kalivanthapattu, Baburayanpettai, Minnal Chithamur, Kilathivakkam and Chunambedu.

The fundamental details will include information on the number of panchayats (basic governing institution in Indian Villages), anganwadis(Rural child care centre in India), and the demographics of preschool children registered in Anganwadi.

Subsequent to the fundamental data collection and establishment of a rapport with the Panchayat authorities and Anganwadi personnel, a preliminary screening will be conducted by physiotherapists on all Anganwadi children aged between 3 to 5 years in 12 SRM UBA adopted villages after obtaining the parental consent. This screening aims to comprehensively enumerate data for determining the prevalence of Neurodevelopmental Disorders (NDD) among these children. The rapport established with village authorities will help in gaining confidence of common people and will help in improving their adherence.

Physiotherapists, in collaboration with parents, will complete a screening checklist. This checklist will primarily focus on detecting developmental delays, DCD, autism, and ADHD, as these are the most commonly observed NDDs among preschoolers. Information on children previously diagnosed with NDD and their history of treatment/rehabilitation will be gathered retrospectively.

Upon identifying the prevalence of neurodevelopmental disabilities, model centers will be established in villages with high prevalence rates. Consideration will be given to ensuring that these centers are accessible to the entire population, including nearby villages by discussing with the village heads. The establishment of model clinics will be based on the identified needs. While the initial plan is to set up one model center, if the prevalence is high and there is a demand, multiple model centers will be established by clustering the villages based on NDD distribution.

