## Discussion

The anticipated primary outcome of the research will focus on the influence of the model center on reducing the burden among caregivers of children with NDD in the adopted villages affiliated with SRM Institute of Science and Technology, situated in Kattankulathur. Moreover, alongside the dissemination of the research findings, it will facilitate the strategic development of specialized services and the provision of care, as well as the appropriate referral of patients to higher levels of healthcare as necessary.

The Indian government has initiated UBA Scheme for the upliftment of rural villages. The primary objective of the UBA scheme is to engage higher educational institutions in research and understanding the realities of these communities at grass root level to contribute to the development of the village.

SRMIST under UBA has signed a Memorandum of Understanding with the Tamil Nadu State Institute of Rural Development and Panchayat Raj (SIRD&PR). The aim of the MoU was aligned with nine Local Sustainable Developmental Goals (LSDG) which included healthy village and child friendly village.

This research tries to fulfil these objectives by involving health care professionals in village level care via which both hospitals will be benefited by understanding the realities and also the village will be uplifted by reducing disability and caregiver burden. Also, the establishment of local outreach centre will help reducing the time and travel burden of parents making sure that the child receives treatment to the maximum.

The findings of this investigation will yield essential data concerning the frequency of developmental irregularities and disabilities among preschool children in twelve adopted villages linked with SRM, located in Kattankulathur. This data has the potential to steer the formulation of suitable strategies and protocols for the early implementation of rehabilitative measures, thereby alleviating the burden of disability among preschool children.

Furthermore, this study can act as a blueprint for establishing similar centers in various regions within Tamil Nadu. The data gathered will serve as a compass for governmental bodies and healthcare agencies in devising pertinent strategies and protocols to mitigate the prevalence of disability among children in Tamil Nadu.

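### NDD prevalence is promised for children in the twelve villages, but only Anganwadi children, described inconsistently as registered or attending, are screened

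*Protocol article*

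**What the plan says.** The protocol article uses a wide population when it states what will be learned:

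- Primary objectives, first objective: "To assess the prevalence of neurodevelopment disorder among children in the UBA adopted villages of SRMIST". There is no Anganwadi restriction.
- Discussion, promised finding: "the frequency of developmental irregularities and disabilities among preschool children in twelve adopted villages". Again there is no restriction. The aim that closes the Background is equally wide.

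It uses a narrower population, worded in three ways, when it states what will be done:

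- Abstract, Methods: "screening all preschool children registered in Anganwadi in the designated villages".
- Participants: "children aged 3 to 5 years attending Anganwadi centers in SRM UBA adopted villages", screened with parental consent.
- Procedures: "a preliminary screening will be conducted by physiotherapists on all Anganwadi children aged between 3 to 5 years in 12 SRM UBA adopted villages", after parental consent, with the purpose of "determining the prevalence of Neurodevelopmental Disorders (NDD) among these children".

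The first-phase data listed in Procedures include "the demographics of preschool children registered in Anganwadi". No count of all village children is listed.

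**The concern.** A prevalence needs one population for numerator and denominator, and it should be the population named in the conclusion. Here the conclusion names village children and the method names Anganwadi children. Within the method, *registered* and *attending* can be different sets.

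The figure has consequences. It is a primary objective. Under Procedures it guides which villages receive a model centre and whether there is more than one. Table 1 places sharing of findings with authorities in the same column as the prevalence analysis, and the Abstract and Discussion offer the data to government for policy. The Background argues that barriers to access keep children from care, so a frame that depends on enrolment at, or attendance of, a centre deserves care in this study.

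**Working it through.** **Step 1. Compare the populations.**

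| Section | Population named | Role |
|---|---|---|
| Primary objectives | Children in the adopted villages | Target |
| Discussion | Preschool children in the twelve villages | Conclusion |
| Abstract, Methods | Registered in Anganwadi | Screened |
| Participants | Attending Anganwadi, aged 3 to 5, consent | Screened |
| Procedures | All Anganwadi children aged 3 to 5, consent | Screened, and the group the prevalence refers to |
| Procedures, first phase | Registered in Anganwadi | Enumerated |

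No row links the last four to the first two. Participants also includes previously diagnosed children, but in the context of the same Anganwadi base, and no community route for finding them is described.

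**Step 2. What the mismatch could do to a village figure.** The article states no sample size or precision for the prevalence, so there is no figure of the plan's own to reproduce. Let p be the prevalence among covered children, c the share of village children covered, and R the rate in uncovered children relative to covered ones. Then

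village prevalence = c·p + (1 − c)·R·p.

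Input p = 12.5% is the Abstract's 1 in 8, used only as an example. Both c and R are assumptions, since the article gives neither.

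| c | R | Village prevalence | Observed / village |
|---|---|---|---|
| any | 1 | 12.5% | 1.00 |
| 0.9 | 2 | 0.9 × 12.5 + 0.1 × 25 = 13.75% | 0.91 |
| 0.9 | 3 | 0.9 × 12.5 + 0.1 × 37.5 = 15.0% | 0.83 |
| 0.7 | 2 | 0.7 × 12.5 + 0.3 × 25 = 16.25% | 0.77 |
| 0.7 | 3 | 0.7 × 12.5 + 0.3 × 37.5 = 20.0% | 0.63 |
| 0.7 | 0.5 | 0.7 × 12.5 + 0.3 × 6.25 = 10.6% | 1.18 |

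The last row shows that the error reverses when R is below 1. The ratios do not depend on p. With the Background's 2% as the observed value, the R = 2 to 3 rows run from 2.2% to 3.2%.

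**Step 3. Registered against screened.** Let N children be registered, n screened, and x found with NDD. With nothing assumed about the unscreened, the prevalence among registered children lies between x/N and (x + N − n)/N. Assume 12.5% among the screened:

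- 95% screened: lower 0.95 × 12.5 = 11.9%; upper 11.9 + 5 = 16.9%.
- 80% screened: lower 0.80 × 12.5 = 10.0%; upper 10.0 + 20 = 30.0%.

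Reporting x/N alone counts every unscreened child as free of NDD, which is the lower bound. Reporting x/n alone assumes the unscreened have the same rate. The two answers differ (10.0% against 12.5% at 80% screened), and the present wording does not say which is meant.

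**The case against.** The strongest reply is that Procedures, the operative section, already ties the screening prevalence to the Anganwadi children, so the fault is loose wording in a one-line objective and a Discussion sentence of a condensed article. The first part is right: the method is consistent with an Anganwadi prevalence. That does not remove the conflict, because the objective and the promised finding are what authorities will read, and a fuller document would not make these sentences agree.

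The three descriptions might also be everyday synonyms. That is possible, and the article does not say that the denominator will be attenders or that it will be the register. The point is only that the reader cannot tell.

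Three stronger readings are tempting, and the text does not support them.

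- *The most disabled children are the ones left out, so prevalence will be underestimated.* This is plausible, but no section gives Anganwadi coverage, attendance by disability or NDD rates outside the Anganwadis. The error may be zero or may run the other way.
- *Registered absentees will not be screened.* The checklist is completed with parents, and three of the tools are described as parental, parent-administered or parent-rated. Nothing restricts screening to children present on the day.
- *Centres will be sited wrongly.* Similar coverage across villages at a common R leaves their ranking unchanged. Siting also depends on need, demand and discussion with village heads about access. A distortion needs coverage, or R, to differ between villages, and the article is silent on that.

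**Conclusion.** The point holds as a mismatch between the claimed and the screened population, together with inconsistent naming of the screened one. As designed, the study can estimate prevalence among consenting Anganwadi children aged 3 to 5. It cannot support a prevalence for all preschool children in the twelve villages.

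The size is not known. The 13.75% to 20% range rests entirely on assumed coverage of 70% to 90% and an assumed rate ratio of 2 to 3. It shows that the mismatch could matter, and it is not evidence that the reported figure will be too low. The correction is worth making because prevalence is a primary objective with practical use and the remedy is nearly free.

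**What to change.** 1. In the Abstract, Participants and Procedures, name one frame and one denominator: children aged 3 to 5 on the Anganwadi registers of the twelve villages, as collected in phase 1.
2. For each village and overall, report the numbers registered (N), screened (n) and found with NDD (x). Give the bounds x/N and (x + N − n)/N, which treat unscreened registered children, including those without consent, as missing. If x/n is shown, state that it assumes the same rate in the unscreened.
3. Restrict the first primary objective and the Discussion's promised finding to prevalence among Anganwadi-registered children aged 3 to 5 in the adopted villages.
4. State as a limitation that children outside the Anganwadis are not measured and may have a higher or a lower rate.

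The cost is a few sentences and a count table built from registers that phase 1 already collects. The downside is a narrower stated population: rewording makes the claim match the data but does not reach children outside the Anganwadis. A village-wide claim would need a count of all preschool children and screening outside the Anganwadis, which is a larger undertaking.
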